## 8.3 Study procedures

### Summary of study procedures

#### Pre-operatively

- Description of (burn)wounds; cause, cooling, %TBSA, etc.
- Clinical depth assessment by (plastic) surgeon / burn physicians and laser Doppler imaging, in case of burn wounds, between day 2 and 5 post-burn.
- Digital photographs of all (burn) wounds and especially of target wounds.
- Until operation (burn) wounds are treated according to local protocol.

#### Per-operatively

- Prior to skin grafting debridement(s) and/or allograft applications are performed to prepare wound beds for skin grafting.
- Target wounds will be marked with part A or B with a minimum of 36 cm^2 per wound.
- Digital photographs will be taken of the target wounds.
- Wound swabs for microbiological analysis will be harvested from the wound bed of each target wound before cleaning the wound.
- Randomisation will follow and target wounds will be grafted with the micrografting .technique and the meshed graft technique. Skin grafting techniques are further explained

below (8.3 skin grafting techniques).

#### Post-operatively and follow-up

- Assessment of study objectives (see section 2 objectives) will be performed during admission in burn centre and several objectives will be assessed at the outpatient clinic 3 and 12 months after operation (see below section 8.3 Follow-up).

### **Skin grafting techniques**

#### Micrografting

First debridement of the (burn) wounds to be grafted is performed according to local protocol, until a vital wound bed shows. Hemostasis is secured. The surface area of the to be grafted wounds is estimated by the amount of cork squares (42x42 mm) that matches the total wound bed. Thereafter, split thickness skin graft (SSG) of 0.1mm is harvested with the Zimmer dermatome from the in advance selected donorsite area. After harvesting, an alginate wound dressing with adrenaline suspension is placed on the donorsite and the SSG is placed with the dermal site on cork square and cut off. This procedure is repeated until the whole SSG is divided over cork squares, including all small graft fragments. Next, the cork fragments are placed in a holder and passed through the cutting machine. The SSG is cut in 14 long stripes of 3 mm wide. The cork square is now rotated for 90° and passed through the cutting machine again, the graft is now subdivided in little 196 squares of 3x3 mm. Now adhesive spray is applied on the epidermal (upper) site of the graft. When the graft is dried, the cork square is pressed on a double layered pre-folded gauze (plissee). Subsequently, the cork square is removed, which leaves all graft squares on the plissee. Expansion is obtained by traction on all four sides of the plissee, expansion ratio depends on plissee size. The firm supportive layer of the plissee is then removed, leaving a single layered gauze with 196 separated graft squares.

[figure not shown]

Meek surgery - <https://ozmedix.com.au/humeca/meek/>

Finally, all single layered plissees are placed with dermal side onto the wound bed and fixated with staplers. Afterwards all ensured plissees are covered with antibacterial gauzes and topped with dry sterile gauzes and bandages. Donorsite is treated with a foam wound dressing with stays on the wound for 14 days. First wound inspection will be conducted after at 8 +/- 2 days to assess the take rate of the graft. Hereafter, daily wound dressing changes will be performed. All residual effects will be treated according to the local standard of care.

#### Meshed grafting

Debridement of the wound bed, harvesting of the SSG and wound care of the donorsite will be performed according to similar procedure as for micrografting. Next, SSG will be placed on a dermacarrier and the meshing machine is set to the preferred expansion ratio. Then the dermacarrier with SSG is passed through the meshing machine. Multiple perforations are made into the SSG, which enables expansion of the graft. Meshed graft will be attached to the wound bed (dermal side down) and fixated with staplers. Finally, the meshed grafts are covered with (antibacterial) gauzes and topped with dry sterile gauzes and bandages.

[figure not shown]

Augustine, R. et al. Advancement of wound care from grafts to bioengineered smart skin substitutes, 2014, Progress in Biomaterials, 3, 103-113

## Follow-up

### Measurements 3 and 12 months after operation

- Regular check-up after hospital discharge
- Preference skin grafting technique
  - Question preference of patient regarding skin grafting technique on this moment
- Scar quality:
  - Patient and Observer Scar Assessment Scale
  - Scar color and pigmentation measurement with Mexameter or Dermaspectrometer
  - Scar elasticity measurement with Cutometer
- Mobility
  - Questionnaire - Quick Disabilities of the Arm, Shoulder and Hand (Quick DASH) - for (burn)wounds concerning upper extremity
  - Questionnaire - Lower Extremity Functional Scale (LEFS) - for (burn)wounds concerning lower extremity
  - Objective measurement of range of motion with a goniometer
- Quality of life
  - Questionnaire - EQ5D-5L
  - Questionnaire - Short Form Health Survey 36-item (SF36)
  - Questionnaire - Dermatology Life Quality Index (DLQI)

## 8.4 Withdrawal of individual subjects

Subjects can leave the study at any time for any reason if they wish to do so without any consequences. The investigator can decide to withdraw a subject from the study for urgent medical reasons.

### 8.4.1 Specific criteria for withdrawal (if applicable)

Not applicable

### **8.5 Replacement of individual subjects after withdrawal**

There will be no replacement of individual subjects after withdrawal.

### **8.6 Follow-up of subjects withdrawn from treatment**

Subjects withdrawn from the study will receive every treatment as usual and all the follow ups and after care as foreseen for every other burn patient.

### **8.7 Premature termination of the study**

No criteria are foreseen for premature termination of the study.

## 9. SAFETY REPORTING

### 9.1 Temporary halt for reasons of subject safety

In accordance to section 10, subsection 4, of the WMO, the sponsor will suspend the study if there is sufficient ground that continuation of the study will jeopardise subject health or safety. The sponsor will notify the accredited METC without undue delay of a temporary halt including the reason for such an action. The study will be suspended pending a further positive decision by the accredited METC. The investigator will take care that all subjects are kept informed.

### 9.2 AEs, SAEs and SUSARs

#### 9.2.1 Adverse events (AEs)

Adverse events are defined as any undesirable experience occurring to a subject during the study. Known adverse events in burn treatment, including both skin grafting techniques, include:

- Post-operative pain
- Post-operative bleeding
- Wound infection
- Impaired healing of donorsite
- Reduced rate of epithelisation of skin graft

The aim of this study is to compare both skin grafting techniques. Therefore these adverse events are not related to the study and will not be reported as adverse events. They will be monitored and listed as secondary outcome parameters.

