### Secondary Objectives:

- To assess donorsite morbidity, wound healing, epithelisation, mobility and quality of life after skin grafting with micrografting versus mesh grafting.

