#### 8.1.2 Secondary study parameters/endpoints (if applicable)

- Long-term scar quality 3 and 12 months after skin transplantation
  - Subjective measurement of scar quality with Patient and Observer Scar Assessment Scale (POSAS). This is based on multiple aspects of scar formation such as: vascularization, pigmentation, texture, thickness, pliability, itch and pain, and is performed by member of research team and by patient.
  - Objective measurements of scar color and pigmentation with the Mexameter or Dermaspectrometer. Skin elasticity is objectively measured with the Cutometer.
- Skin graft technique preferred by patient
  - Patient gives overall indication as to what skin graft technique he/she would prefer if he/she were to require skin grafting again: weekly during admission, and at 3 and 12 months follow up
- Donorsite size and ratio of donorsite size and actual graft size (cm^2)
  - Surface areas will be calculated with a 3D-camera (Woundworks inSight)
- Take rate of skin grafts
  - Take rate will be clinically assessed at 8 +/- 2 days and expressed as the percentage of micrografted and meshed graft take
- Healing time
  - Clinical assessment of wound healing 14 and 21 days +/- 2 post application expressed as percentage of the total wound surface area healed
  - Time to complete wound closure where complete wound closure is defined as > 95% re-epithelialization of the wound with the absence of drainage and no longer needing a substantial wound dressing
- Bacterial load
  - Wound swabs for semi-quantitative investigation
  - Semi-quantitative bacteriology in both groups
  - Percentage of patients within both groups with clinical wound infection requiring systemic antimicrobial therapy
  - 'Clinical infection' is defined as the presence of cellulitis and/or visible purulence and/or lymphangitis combined with one or more of the following: local wound pain/erythema/edema/malodor

- Pain
  - Will be evaluated in the autografted target wounds with help of a Visual Analogue Scale (VAS score) on day 2 post surgery, before and after removal of Surfasoft®/Urgotul in case of meshed skin grafts or plissees in case of micrografting, and thereafter once weekly during the hospitalization period. After hospital discharge pain will be evaluated again at the 3 and 12 months follow ups
- Number of secondary procedures
  - Re-interventions in study areas due to insufficient take or necessity of reconstructive surgery
- Mobility at 3 and 12 months

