#### 9.2.2 Serious adverse events (SAEs)

A serious adverse event is any untoward medical occurrence or effect that

- results in death;
- is life threatening (at the time of the event);
- requires or prolongs inpatient (unexpected) hospitalization ;

An elective hospital admission will not be considered as a serious adverse event.

The sponsor will report these SAEs through the web portal *ToetsingOnline* to the accredited METC that approved the protocol, within 7 days of first knowledge for SAEs that result in death or are life threatening followed by a period of maximum of 8 days to complete the initial preliminary report. All other SAEs will be reported within a period of maximum 15 days after the sponsor has first knowledge of the serious adverse events.

Serious adverse events that can occur after surgical treatment in general are defined as; any untoward medical occurrence or effect that results in:

- Pneumonia;
- Urinary tract infections;
- Sepsis;
- Pulmonary embolism;
- Re-operation

**9.2.3 Since the aim of this study is to compare both skin grafting techniques, these serious adverse events are probably not related to the study. However, these SAEs are serious by its nature and therefore will be reported yearly to the METc through a line listing. Suspected unexpected serious adverse reactions (SUSARs)**

There are no SUSARs expected during this study. No additional risks on adverse events are expected, seen both skin grafting techniques are already frequently used in daily practice of (burn) wounds. In case there is unexpected events which meets the criteria of a SUSAR the sponsor will report expedited the following SUSARs through the web portal *ToetsingOnline* to the METC *<reporting via webportalToetsingOnline is only applicable for investigator initiated studies>*:

- SUSARs that have arisen in the clinical trial that was assessed by the METC;
- SUSARs that have arisen in other clinical trials of the same sponsor and with the same medicinal product, and that could have consequences for the safety of the subjects involved in the clinical trial that was assessed by the METC.

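### Two of the five complications that section 9.2.1 takes out of adverse event reporting have no endpoint in 8.1.2, and the yearly SAE listing is not reconciled with the 7- and 15-day terms

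*Protocol*

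**What the plan says.** **Exempted complications.** Protocol section 9.2.1 lists post-operative pain, bleeding, wound infection, impaired donor-site healing and reduced epithelisation of the graft as known events of burn treatment with either technique. It continues: "Therefore these adverse events are not related to the study and will not be reported as adverse events". It then says where they go instead: "They will be monitored and listed as secondary outcome parameters".

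**Donor-site objective.** The secondary objectives in section 2 begin: "To assess donorsite morbidity, wound healing, epithelisation". In section 8.1.2 the donor-site item is size and the ratio of donor-site size to graft size. Of pain, 8.1.2 says: "Will be evaluated in the autografted target wounds with help of a Visual Analogue Scale".

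**Serious events.** Section 9.2.2 defines an SAE by death, threat to life, or new or prolonged hospital stay. Fatal and life-threatening SAEs go to the ethics committee within 7 days, with 8 more days to complete the report. For the rest: "All other SAEs will be reported within a period of maximum 15 days". The section then names pneumonia, urinary tract infection, sepsis, pulmonary embolism and re-operation as SAEs that can follow surgery in general. Of these it says (in text that has run into the heading of 9.2.3): "these SAEs are serious by its nature and therefore will be reported yearly to the METc through a line listing". Section 8.1.2 makes the same split, direct reporting for the first group and a yearly list for the second.

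**The concern.** The exemption in 9.2.1 is sound only if every exempted event is recorded as an outcome. Where 8.1.2 has no matching item, the event is barred from one record and absent from the other. A later analysis plan cannot repair this, because it cannot analyse what was not collected.

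Donor-site complications matter to this trial's own argument. The introduction says donor-site problems often hurt patients more in the short term than the burn does, and it describes the trial as evaluating a reduction in donor-site morbidity.

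For serious events, two centres in two countries could each follow the text and report the same event on different terms. The protocol has no DSMB (9.5), no monitoring (12.2) and no criteria for early termination (8.7), so section 9.2 is the main safety route.

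**Working it through.** No sample size, error rate or event count enters this point, so the check is a comparison of sections.

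**Step 1. The five exempted events (9.2.1) against the secondary endpoints (8.1.2).**

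| Event in 9.2.1 | Item in 8.1.2 | Covered? |
|---|---|---|
| Post-operative pain | VAS, grafted wounds only | Yes, for the grafted wound |
| "Post-operative bleeding" | None | No |
| Wound infection | Clinical infection needing systemic therapy; swabs | Yes |
| "Impaired healing of donorsite" | None; only donor-site size and ratio | No |
| Reduced epithelisation of the graft | Take, percentage healed, time to closure | Yes |

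Covered: 3 of 5. Not covered: 5 − 3 = 2.

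**Step 2. Could another item catch the two?**
- The healing assessments at days 14 and 21 are timed from graft application and concern the grafted wound, not the donor site.
- The count of secondary procedures is limited to insufficient take and reconstructive surgery, so it does not count bleeding as such.
- The endpoint on AE and SAE incidence cannot count events that 9.2.1 says are not reported as AEs.
- The other parameters in 8.1.3 include neither.
- The SAE rules in 9.2.2 do catch a bleed that threatens life, prolongs the stay or leads to re-operation.

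What is left without a defined record is non-serious bleeding and impaired donor-site healing.

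**Step 3. What measures donor-site morbidity?** Size and ratio are measured. Donor-site pain is not, because the VAS is tied to the grafted wounds. Donor-site healing is not (step 1). The quality-of-life questionnaires are answered once per patient, and each patient receives both techniques, so they cannot be attributed to one technique. The objective therefore rests on size and ratio alone.

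**Step 4. The two SAE terms.**

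| Event | General rule in 9.2.2 | Surgical list in 9.2.2 |
|---|---|---|
| Listed event, fatal or life-threatening | 7 days (+8 to complete) | Yearly |
| Listed event that requires or prolongs hospital stay | 15 days | Yearly |
| Listed event meeting none of these criteria | Not clearly covered | Yearly |

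The first two rows fall under both rules. This applies to all five listed events. No sentence in 8.1.2 or 9.2.2 says whether the yearly list replaces the expedited terms or adds to them.

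**The case against.** The other side has substantial points.

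- *The events are not discarded.* Section 9.2.1 commits to monitoring them, and the CRF is not shown, so actual loss of data is an inference. This stands. A reader might infer that the two complications are recorded nowhere at all. The documents do not support that, because serious bleeds remain reportable as SAEs. The gap is confined to non-serious bleeding and donor-site healing.
- *The donor-site hypothesis has data.* The summary objective and the stated hypothesis concern donor-site size, which is measured. This also stands, so it would be wrong to say that the trial's main donor-site claim lacks data. But section 2 names morbidity, which is broader than size.
- *The two SAE rules are compatible.* Nothing says the listed events are reported only yearly, and the list may be additional. This is a fair reading. A reader might infer that the protocol lets a life-threatening sepsis wait up to a year, but that is only the worst reading of an open text. What stands is that the text does not choose.
- *Re-operation is already an outcome.* A reader might infer that calling surgical SAEs probably unrelated hides failed grafts. It does not: 8.1.2 counts re-interventions in the study areas for insufficient take or reconstruction, and those areas are the randomised units.
- *Harvest and donor-site care are the same for both techniques.* This is correct, and the protocol does not say whether each technique has its own distinct donor site. A difference in donor-site complications is therefore possible but not shown, and recording by technique may not always be feasible.

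**Conclusion.** The point holds in limited form. Two of the five exempted complications have no counterpart among the secondary endpoints, and the morbidity objective is measured by size and ratio only. For all five listed surgical SAEs, the governing term is undefined when the event also meets a general SAE criterion. It could be 7 or 15 days or, on one reading, up to about a year.

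This rests on the protocol alone and assumes that the CRF follows 8.1.2. If the CRF already has fields for bleeding and donor-site healing, the first part reduces to aligning the text. The primary endpoint and its analysis are unaffected. The inconsistency should be fixed, preferably before enrolment, because unrecorded complications cannot be reliably recovered afterwards.

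**What to change.** 1. Add post-operative bleeding and donor-site healing to 8.1.2 and the CRF, recorded by technique where the donor sites can be told apart. Add a donor-site check around the planned day 14 and 21 assessments; this is a new assessment, since the existing ones concern the grafted wound. If morbidity remains an objective, add donor-site pain as well.
2. Otherwise, delete the exemption in 9.2.1 for these two events and keep them in AE reporting.
3. Reconcile 8.1.2 with 9.2.2 by one sentence stating how the yearly listing relates to expedited reporting when a listed event is also fatal, life-threatening, or requires or prolongs hospital stay. Which term governs is for the sponsor and the ethics committee to decide.

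The cost is a few CRF fields, a short additional donor-site check and slightly more reporting work.

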#### 9.2.2 Serious adverse events (SAEs)

A serious adverse event is any untoward medical occurrence or effect that

- results in death;
- is life threatening (at the time of the event);
- requires or prolongs inpatient (unexpected) hospitalization ;

An elective hospital admission will not be considered as a serious adverse event.

The sponsor will report these SAEs through the web portal *ToetsingOnline* to the accredited METC that approved the protocol, within 7 days of first knowledge for SAEs that result in death or are life threatening followed by a period of maximum of 8 days to complete the initial preliminary report. All other SAEs will be reported within a period of maximum 15 days after the sponsor has first knowledge of the serious adverse events.

Serious adverse events that can occur after surgical treatment in general are defined as; any untoward medical occurrence or effect that results in:

- Pneumonia;
- Urinary tract infections;
- Sepsis;
- Pulmonary embolism;
- Re-operation

**9.2.3 Since the aim of this study is to compare both skin grafting techniques, these serious adverse events are probably not related to the study. However, these SAEs are serious by its nature and therefore will be reported yearly to the METc through a line listing. Suspected unexpected serious adverse reactions (SUSARs)**

There are no SUSARs expected during this study. No additional risks on adverse events are expected, seen both skin grafting techniques are already frequently used in daily practice of (burn) wounds. In case there is unexpected events which meets the criteria of a SUSAR the sponsor will report expedited the following SUSARs through the web portal *ToetsingOnline* to the METC *<reporting via webportalToetsingOnline is only applicable for investigator initiated studies>*:

- SUSARs that have arisen in the clinical trial that was assessed by the METC;
- SUSARs that have arisen in other clinical trials of the same sponsor and with the same medicinal product, and that could have consequences for the safety of the subjects involved in the clinical trial that was assessed by the METC.

The remaining SUSARs are recorded in an overview list (line-listing) that will be submitted once every half year to the METC. This line-listing provides an overview of all SUSARs from the study medicine, accompanied by a brief report highlighting the main points of concern. The expedited reporting of SUSARs through the web portal Eudravigilance or ToetsingOnline is sufficient as notification to the competent authority.

The sponsor will report expedited all SUSARs to the competent authorities in other Member States, according to the requirements of the Member States.

The expedited reporting will occur not later than 15 days after the sponsor has first knowledge of the adverse reactions. For fatal or life threatening cases the term will be maximal 7 days for a preliminary report with another 8 days for completion of the report. is will be reported

### **9.3 Annual safety report**

In addition to the expedited reporting of SUSARs, the sponsor will submit, once a year throughout the clinical trial, a safety report to the accredited METC, competent authority, and competent authorities of the concerned Member States.

This safety report consists of:

- a list of all suspected (unexpected or expected) serious adverse reactions, along with an aggregated summary table of all reported serious adverse reactions, ordered by organ system, per study;
- a report concerning the safety of the subjects, consisting of a complete safety analysis and an evaluation of the balance between the efficacy and the harmfulness of the medicine under investigation.

### **9.4 Follow-up of adverse events**

All AEs will be followed until they have abated, or until a stable situation has been reached. Depending on the event, follow up may require additional tests or medical procedures as indicated, and/or referral to the general physician or a medical specialist.

SAEs need to be reported till end of study within the Netherlands, as defined in the protocol

